# A multicenter, open-label, randomized, proof-of-concept phase II clinical trial to assess the efficacy and safety of icatibant in patients infected with SARS-CoV-2 (COVID-19) and admitted to hospital units without invasive mechanical ventilation: study protocol (ICAT-COVID)

**DOI:** 10.1186/s13063-022-06219-7

**Published:** 2022-04-12

**Keywords:** SARS, ACE2, ARDS, Bradykinin, SARS-CoV-2, COVID-19, Icatibant

## Abstract

**Background:**

COVID-19 has quickly become a global pandemic with a substantial number of deaths and is a considerable burden for healthcare systems worldwide. Although most cases are paucisymptomatic and limited to the viral infection-related symptoms, some patients evolve to a second phase, with an impaired inflammatory response (cytokine storm) that may lead to acute respiratory distress syndrome and death. This is thought to be caused by increased bradykinin synthesis.

**Methods:**

ICAT-COVID is a multicenter, randomized, open-label, proof-of-concept phase II clinical trial assessing the clinical efficacy and safety of adding icatibant to the standard of care in patients hospitalized with COVID-19 without invasive mechanical ventilation. Patients hospitalized with a confirmed COVID-19 pneumonia diagnosis (RT-PCR or antigen test ≤ 10 days prior to randomization, and radiographic evidence of pulmonary infiltrates), rated “4” or “5” on the WHO’s clinical status scale, are eligible. Patients will be randomized on a 1:1 ratio to either standard of care-plus-icatibant (experimental group) or to standard of care alone (control group). The experimental group will receive 30 mg of icatibant subcutaneously 3 times a day for 3 days (for a total of 9 doses). The expected sample size is 120 patients (60 per group) from 2 sites in Spain. Primary outcomes are the efficacy and safety of Icatibant. The main efficacy outcome is the number of patients reaching grades “2” or “1” on the WHO scale within 10 days of starting treatment. Secondary outcomes include “long-term efficacy”: number of patients discharged who do not present COVID-19-related relapse or comorbidity up until 28 days after discharge, and mortality.

**Discussion:**

Icatibant, a bradykinin type 2 receptor antagonist with proven effectiveness and safety against hereditary angioedema attacks, may be beneficial for COVID-19 patients by inhibiting bradykinin’s action on endothelial cells and by inhibiting the SARS-CoV-2 M protease. Our working hypothesis is that treatment with standard of care-plus-icatibant is effective and safe to treat patients infected with SARS-CoV-2 admitted to hospital for pneumonia without invasive mechanical ventilation.

**Trial registration:**

EudraCT 2020-002166-13. ClinicalTrials.gov NCT04978051

**Supplementary Information:**

The online version contains supplementary material available at 10.1186/s13063-022-06219-7.

## Introduction

### Background and rationale {6a}

The disease caused by the novel coronavirus SARS-CoV-2 (COVID-19) has become a global pandemic [1]. Since the start of the pandemic in March 2020, until January 31, 2022, the World Health Organization (WHO) has confirmed 380,321,615 cases and 5,680,741 deaths worldwide [2]. For the medical community, this new disease represents a challenge in identifying effective therapeutic options for treatment and prevention.

Multiple randomized clinical trials on COVID-19 are currently ongoing, and a wide range of drugs are being administered in clinical practice to adequately address the two clinical phases that the disease appears to have in its most severe manifestation: a first phase with viral infection predominance and a second phase with an exacerbated inflammatory response predominance [3], which causes, in most cases, acute respiratory distress syndrome (ARDS) in adult patients.

Icatibant acetate (Firazyr®) is a synthetic peptide, similar in structure to bradykinin, that acts as a competitive antagonist at the bradykinin type 2 receptor (BKB2R) on the endothelial cells [4]. Icatibant is approved for the treatment of acute attacks of angioedema in patients diagnosed with hereditary angioedema (HAE) [5, 6]. Its long-term safety has been proven with data from the Icatibant Outcome Survey: IOS registry [7, 8]. Icatibant has also been shown to be effective against ACE inhibitor-induced angioedema in some case series, as well as in real-life clinical experience [9]. It is noteworthy that ACE inhibitors-induced angioedema has bradykinergic characteristics and does not respond to corticosteroids, antihistamines or epinephrine.

Since the contact system is activated in ARDS, there is an increased bradykinin synthesis that triggers a local pulmonary inflammatory response due to activation of the bradykinin receptors of endothelial cell [10]. This increases vascular permeability and recruitment and activation of inflammatory mediators, causing the pulmonary edema seen in the disease’s early stages [11]. Moreover, SARS-CoV-2 binding to the respiratory epithelial cells’ ACE2 receptor decreases its activity [12], increasing plasmatic levels of des-Arg9-bradykinin, although a Chinese cohort study did not find an increased risk of infection with SARS-CoV-2 in hypertensive patients treated with ACE inhibitors [13].

The rationale for the potential efficacy of icatibant in COVID-19 is based on the inhibition of the action of bradykinin on endothelial cells and on the inhibition of the SARS-CoV-2 M protease (a key enzyme in coronavirus replication). This last mechanism of action was identified on a theoretical computational model [13]. Our working hypothesis is that adding icatibant to standard of care (SoC) is effective and safe in patients with pneumonia caused by SARS-CoV-2 (COVID-19) without invasive mechanical ventilation and admitted to hospital units. The purpose of this project is to conduct a proof-of-concept, multicenter, controlled, randomized clinical trial to provide the first evidence of our working hypothesis.

### Explanation for the choice of comparators {6b}

In January 2021, SoC, based on respiratory support measures, fluid therapy, antipyretic treatment, postural measures, low-molecular-weight-heparins, corticosteroids (such as dexamethasone), and remdesivir (put in question), was the treatment of choice. With the appearance of new potential treatments during the study, we allow the use of every authorized drug as standard of care [14] in order to offer the best treatment to patients.

In this clinical trial, therefore, adding icatibant to SoC will be compared to SoC alone for hospitalized COVID-19 patients with pneumonia caused by SARS-CoV-2 (COVID-19) without invasive mechanical ventilation.

### Objectives {7}

#### Primary objective

The main objective of the ICAT-COVID study is to assess the efficacy and safety of icatibant 10 days after starting treatment (or at hospital discharge if this occurs before) in adult inpatients with SARS-CoV-2 pneumonia and without invasive mechanical ventilation.

#### Secondary objectives

The secondary objectives are as follows: (1) to study the time to achieve a sustained clinical response for 48 h, (2) to study the time to reach a sustained afebrile state for 48 h, (3) to study long-term efficacy 28 (± 3) days after hospital discharge, (4) to study the role of pharmacological treatments used in SoC in efficacy and safety, (5) to quantify hospital stay duration (in days), (6) to assess the influence of elapsed time from symptom onset (days with the disease) on treatment response, (7) to assess the incidence of COVID-19-related complications up to 28 (±3) days after hospital discharge, (8) to assess the incidence of SARS-CoV-2 pneumonia relapse from hospital discharge up until 28 (±3) days later, (9) to estimate the incidence of all-cause new emergency room visits from hospital discharge until 28 (±3) days later, (10) to estimate the incidence of mortality due to COVID-19 up to 28 (±3) days after hospital discharge, (11) to estimate the incidence of all-cause mortality through 28 (±3) days after hospital discharge, and (12) to estimate the incidence of adverse events (AEs) by severity up to 28 (±3) days after hospital discharge. To evaluate the safety of icatibant: incidence of adverse events by severity up to 28 (±3) days after hospital discharge.

### Trial design {8}

This study is a phase II, randomized, controlled, open-label, proof of concept, multicenter clinical trial with two parallel groups (experimental group: SoC-plus-Icatibant, and control group: SoC) to assess the efficacy and safety of icatibant in patients with COVID-19 pneumonia without invasive mechanical ventilation, and admitted to hospital units. The outcomes of the study protocol are based on the draft master protocol of the WHO for clinical trials that evaluate the efficacy and safety of investigational therapeutics for the treatment of COVID-19 in hospitalized patients (Table 1) [15].

**Table 1 Tab1:** WHO 8-point ordinal scale for clinical status assessment

Patient status	Score
Uninfected: No clinical or virological evidence of infection	**0**
Ambulatory, with no limitation of activities.	**1**
Ambulatory, with limitation of activities.	**2**
Hospitalized, not requiring supplemental oxygen	**3**
Hospitalized, requiring low-flow supplemental oxygen (mask or nasal prongs)	**4**
Hospitalized, on non-invasive ventilation or high-flow oxygen devices.	**5**
Hospitalized, intubated and mechanical ventilation.	**6**
Hospitalized, on invasive mechanical ventilation and additional organ support: extracorporeal membrane oxygenation (ECMO), renal replacement therapy, pressors.	**7**
Death	**8**

Patients enrolled in the study will be randomly assigned at a 1:1 ratio to the experimental group and the control group. The experimental treatment will consist of SoC-plus-Icatibant (3 doses per day for 3 consecutive days (a total of 9 doses). Each dose will consist of 30-mg icatibant administered subcutaneously. The control treatment will consist of SoC only.

Since the beginning of the COVID-19 pandemic, SoC has been mostly supportive, considering the lack of evidence for highly effective therapies. So SoC could vary depending on the scientific evidence available during the study. In this clinical trial (ICAT-COVID), SoC could include respiratory support measures, fluid therapy, antipyretic treatment, postural measures, low-molecular-weight-heparins, corticosteroids such as dexamethasone, remdesivir, and other therapeutic options.

The diagnosis of SARS-CoV-2 pneumonia will be made in hospitalized patients presenting de novo radiographic infiltrates (either by plain chest radiography or computed tomography), and a confirmed SARS-CoV-2 infection as determined by RT-PCR or antigen test for SARS-CoV-2. Clinical status will be assessed using the WHO 8-point ordinal scale for clinical assessment (Table 1).

## Methods: participants, interventions, and outcomes

### Study settings {9}

ICAT-COVID will be carried out at 2 Spanish healthcare centers:
Bellvitge University Hospital, L’Hospitalet de Llobregat, SpainMartorell Hospital, Martorell, Spain

### Eligibility criteria {10}

*Inclusion criteria:*
Adult patients (≥ 18 years old), of both genders.SARS-CoV-2 infection confirmed by laboratory RT-PCR or antigen test ≤ 10 days prior to randomization.Hospitalized with a diagnosis of SARS-CoV-2 pneumonia.Radiographic evidence of pulmonary infiltrates of ≤ 48.Patients rated “4” or “5” on the WHO 8-point ordinal scale for clinical status assessment.PaO_2_/FiO_2_ < 380.Men and women of childbearing age who have heterosexual intercourse must agree to use safe contraceptive method(s).Subject or legally authorized representative must sign a written informed consent that states that he/she understands and agrees to comply with the planned study procedures.

*Exclusion criteria:*
Imminent death (life expectancy ≤ 24 h)Known hypersensitivity or known adverse reactions to the study drug, its metabolites, or excipients of the formulationInvasive mechanical ventilationParticipation in any other clinical trialALT or AST blood levels > 5 × ULN (upper limit of normal)Creatinine clearance < 50 mL/min using the Cockcroft-Gault formula for participants ≥ 18 years old [13]Patients with a recent acute coronary syndrome (< 1 month)Patients with cerebrovascular accident backgroundWomen who are pregnant or breastfeeding

### Interventions

#### Intervention description {11a}

Takeda has provided the experimental study product: icatibant acetate (Firazyr®, Shire Pharmaceutical Ireland Limited. [name]). The clinical research organization (Bioclever, [name]) engaged for monitoring and pharmacovigilance was in charge of delivering the medication (icatibant) to the hospital pharmacies.

The e-CRF will provide the random code after the investigator introduces the required data. Subsequently, for the first dose, the investigator of each center will contact the person in charge at the hospital pharmacy. Icatibant will be prepared straight after randomization at the hospital pharmacy and the hospital pharmacist will provide it to the nurse in charge of administering it. Subsequent doses (from 2nd to 9th doses) will be scheduled according to usual nursing clinical practice procedure.

As abovementioned (explanation for the choice of comparators {6b} section), in January 2021, SoC was based on respiratory support measures, fluid therapy, antipyretic treatment, postural measures, low-molecular-weight-heparins, corticosteroids (such as dexamethasone), remdesivir, and other therapeutic options. The hospital pharmacy of each center will provide these drugs according to usual clinical practice procedure.

#### Criteria for discontinuing or modifying allocated interventions {11b}

Participants may voluntarily discontinue trial treatment and/or prematurely end their participation in the study for any reason, at any time. The investigator may also decide, at any time during the study, to temporarily interrupt or permanently discontinue the trial treatment if it is deemed that continuation would be detrimental to the participant or not in the best interests of the participant.

Similarly, the sponsor, Ethics Committee (EC), or authorized regulatory authority can decide to halt or prematurely discontinue the clinical trial if new information becomes available whereby the rights, safety, and well-being of trial participants can no longer be assured, when the integrity of the study has been compromised, or when the scientific value of the study has become obsolete and/or unjustifiable.

Circumstances requiring premature treatment interruption or discontinuation of the clinical trial include, but are not limited to, (1) safety concerns related to blood product or unacceptable intolerability (potentially life-threatening reaction during treatment), (2) trial participation while in breach of the eligibility criteria, and (3) pregnancy or the intention of becoming pregnant. In any such case of early trial termination and/or treatment interruption/discontinuation, the investigator will continue to closely monitor the participant’s condition and ensure adequate medical care and follow-up. Additionally, these patients will continue to be followed up for the primary outcome and their data will be included in intention-to-treat analyses.

#### Strategies to improve adherence to interventions {11c}

This study will be carried out on patients admitted to hospital units and treatment will be administered by healthcare professionals under the study team’s supervision. Detailed information on the administration of interventions is provided within the hospital’s electronic system (SILICON) and will be displayed once the nurses administer treatment. Most follow-up visits will be performed during hospital admission. The only visit to be performed on outpatients (visit 7) will be, a priori, a phone call visit, and patients would be requested to come to the hospital for a face-to-face visit only if considered necessary by the evaluating physician.

#### Relevant concomitant care permitted or prohibited during the trial {11d}

##### Concomitant treatment

According to the Summary of Product Characteristics (items 4.3. Contraindications; 4.4. Special warnings and precautions for use; and 4.5. Interaction with other medicinal products and other forms of interaction), icatibant could be administered concomitantly with any drug.

Based on our experience in patients like those proposed to be enrolled in this clinical trial: “patients with SARS-CoV-2 pneumonia with a short time since onset of pneumonia and who need to be admitted to hospital units to be treated with supplemental oxygen using non-invasive ventilation”, approximately 90% of these symptomatic patients with COVID-19 present a self-limited disease course within 7–10 days, and, therefore, are discharged from the hospital (time of the efficacy assessment).

On the other hand, icatibant has a short half-life (1.4 h; within 7–10 h after the last dose, the drug is cleared) and will be administered 3 times a day for 3 days. If the last dose is administered 64 h after the first dose (icatibant administrations at 0, 8, 16, 24, 32, 40, 48, 56, and 64 h), it is expected that at approximately 74 h (start of day four of the trial) icatibant would already be cleared.

One of the main risks for a patient hospitalized for pneumonia and treated with supplemental oxygen through non-invasive ventilation is superinfection (usually bacterial). If this happens during the study, antibiotics may be administered in the first days of the study and are not contraindicated during the use of icatibant.

As a result, the use of any drug will be permitted if considered necessary for clinical management. Any concomitant medication will be recorded in the clinical history (detailing the product, dose, route, days of administration and reason for treatment). All this information will be recorded in the e-CRF.

##### Rescue therapy

If the participant’s condition deteriorates, rescue therapy will be established according to the study protocol of each hospital. In general, these patients will receive the established SoC measures, consisting of respiratory support, fluid therapy, antipyretic treatment, postural measures, and low molecular weight heparins. It may also include anti-inflammatory treatment with corticosteroids, “anti-COVID antivirals” such as remdesivir, and other therapeutic options approved by the authorities.

##### Criteria for the discontinuation of the study treatment

As specified in the Summary of Product Characteristics, icatibant (according to the SmPC for Firazyr®) is contraindicated for hypersensitivity to the active ingredient or to any of its excipients.

### Outcomes {12}

#### Primary outcomes

Primary outcomes are the efficacy and safety of icatibant: number (percentage) of patients considered as responders. Responder is defined as a patient who reaches a clinical response [sustained 48-h grade 2, grade 1, or grade 0 classification on the WHO 8-point ordinal scale for clinical status assessment (Table 1)] *and* who has not presented any severe adverse events (grades “3”, “4,” or “5” of the Common Terminology Criteria for Adverse Events -CTCAE- (Table 2)) within 10 days after starting treatment.

**Table 2 Tab2:** Common Terminology Criteria for Adverse Events (CTCAE) Version 4.0

Classification	Magnitude of the adverse event
**Grade 1**	Mild adverse event. Asymptomatic or mild clinical symptoms or just an observation; intervention not indicated.
**Grade 2**	Moderate adverse event. Minimal, local or non-invasive intervention indicated.
**Grade 3**	Serious or medically significant adverse event, but not immediately life-threatening. Hospitalization or hospitalization prolongation indicated; important limitation of self-care.
**Grade 4**	Adverse event with risk of mortality or disability.
**Grade 5**	Death associated with an adverse event.

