*Visits 2* and *3* will correspond to safety assessment during hospital admission. Visit 2 and visit 3 will take place, respectively, on day 2 (24 h after treatment start, before the 4th dose of icatibant) and on day 3 (48 h after treatment start, before the 7th dose of icatibant). *Visit 4* will take place 72 h after treatment start, end of treatment’ visit (after all doses are administered). Hospital discharge may occur after completing visit 4, if the patient is clinically stable (i.e., no fever for 48 consecutive hours without antipyretic medication, PaO_2_/FiO_2_ > 380 or O_2_ saturation > 94%, respiratory rate ≤ 24 bpm, absence of decompensation of any comorbidity).

*Visit 5* [10 (± 1) days after treatment start] will be an efficacy assessment visit. A clinical assessment will be performed and the patient’s clinical status and clinical stability criteria^#^, as well as the medication used and the presence of adverse events, will be reevaluated. If hospital discharge visit overlaps with the day 10 visit, the investigator will only complete the day 10 visit in the e-CRF, clarifying that it is also the hospital discharge visit. The patient will be sent home and will be informed of the confinement regimen measures to be followed at home (or similar, e.g., medicalized hotel), if necessary.

A patient classified as a treatment failure (i.e., non-responder—any patients who do not meet the criteria to be considered a responder) will have their participation in this study terminated. Afterwards, their condition will be treated at the discretion of the physician in charge of their particular case.

^#^Clinical stability (defined as (1) body temperature ≤ 37.5 °C for 48 h without any antipyretic medication, (2) PO_2_/FiO_2_ > 380 or oxygen saturation > 94%, (3) respiratory rate ≤ 24 rpm, and (4) the absence of any kind of comorbidity decompensation) will also be assessed and the time to achieve it will be calculated starting from the time of the baseline visit.

If the patient is discharged before the 10th day since treatment start, the investigator must complete the day 10 visit in the e-CRF for the efficacy assessment on the same day as hospital discharge.

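### The primary endpoint's 48-hour hold within 10 days implies discharge by about day 8, but the abstract accepts day 10 and the efficacy form is completed on the discharge day, before any of the hold has been observed

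*Protocol article*

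**What the plan says.** - **Outcomes {12}, Primary outcomes.** A responder has a "sustained 48-h grade 2, grade 1, or grade 0 classification on the WHO 8-point ordinal scale for clinical status assessment" and no grade 3, 4 or 5 adverse event, with the limit "within 10 days after starting treatment".
- **Trial design {8}, Table 1.** The worst grade that counts as response is grade 2, "Ambulatory, with limitation of activities". The best grade available to an inpatient is grade 3, "Hospitalized, not requiring supplemental oxygen".
- **Abstract, Methods.** The main efficacy outcome is the number of patients who reach grade 2 or 1 "on the WHO scale within 10 days of starting treatment". There is no 48-hour hold.
- **Objectives {7}, Primary objective.** Efficacy is assessed 10 days after treatment start, or at discharge if that is earlier.
- **Study procedure, visit 5 (day 10 ± 1).** For a patient discharged before day 10, the investigator "must complete the day 10 visit in the e-CRF for the efficacy assessment on the same day as hospital discharge". For a discharge that coincides with day 10: "If hospital discharge visit overlaps with the day 10 visit, the investigator will only complete the day 10 visit in the e-CRF".
- **Concomitant treatment {11d}.** About 90% of such patients are said to have a self-limited course within 7–10 days and "are discharged from the hospital (time of the efficacy assessment").
- **Interim analyses {21b}.** The look takes place once 42 patients have completed 10 days or have been discharged earlier.
- **Plans to promote participant retention {18b}.** Every visit except the last is in hospital. The last is visit 7, 28 days after discharge.

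**The concern.** A 48-hour hold at an out-of-hospital grade cannot have been observed on the day the patient leaves hospital. The outcome definition demands the hold, the abstract leaves it out, and the assessment rules record efficacy before it can have run. Two people who follow this text can classify the same patient differently.

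Three things depend on the classification: the primary response rates and their relative risk, the interim look for efficacy and futility, and the response rate that Sample size {14} intends to use in planning a later superiority trial. A readmission within 48 hours of discharge, which the hold exists to exclude, is also not captured by a form completed on the discharge day.

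**Working it through.** The plan gives no figure to reproduce: Sample size {14} states that no formal estimation was made. The check is date arithmetic followed by an illustration.

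**Step 1: the two cut-offs.** Table 3 counts treatment start as day 0.

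- Hold completed within the limit: latest discharge = limit − 2 days = 10 − 2 = **day 8**.
- If the visit 5 window (day 9 to 11) sets the limit: 9 − 2 = 7 to 11 − 2 = 9, so **day 7 to day 9**.
- Grade only reached within the limit (abstract): latest discharge = **day 10**.

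The definitions are 48 hours apart. This gap does not depend on any assumption about discharge times.

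**Step 2: the same patients under each text (efficacy component only).**

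| Patient | Primary outcomes, hold completed by day 10 | Abstract | Hold observed when the efficacy form is completed |
|---|---|---|---|
| Discharged day 5, stays out | Met | Met | 0 h |
| Discharged day 5, readmitted day 6, not discharged again by day 8 | Not met | Met | 0 h |
| Discharged day 9, stays out | Not met | Met | 0 h |
| Discharged day 10, stays out | Not met | Met | 0 h |

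The last column is 0 h for everyone discharged by day 10. The difficulty of confirming the hold is therefore not confined to discharges between day 8 and day 10.

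**Step 3: how many could change class.** Assume that 90% are discharged by day 10 of treatment. The figure comes from Concomitant treatment {11d}; counting it from treatment start is an assumption, because that section does not give the origin of its 7–10 days. Let F(8) be the share discharged by day 8. The number changing class is 120 × (0.90 − F(8)).

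| Assumed discharge times | F(8) | Gap, points | Of 120 |
|---|---|---|---|
| Lognormal, 2% by day 7 | 0.21 | 69 | 83 |
| Uniform, days 7–10 | 0.90 × 1/3 = 0.30 | 60 | 72 |
| Equal on whole days 7, 8, 9, 10 | 0.90 × 2/4 = 0.45 | 45 | 54 |
| Lognormal, 30% by day 7 | 0.56 | 34 | 41 |
| Uniform, days 3–10 | 0.90 × 5/7 = 0.64 | 26 | 31 |
| Exponential from day 3 | 1 − 0.1^(5/7) = 0.81 | 9 | 11 |
| Exponential from day 0 | 1 − 0.1^(8/10) = 0.84 | 6 | 7 |

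The lognormal rows fix the share by day 10 at 0.90 and the share by day 7 as shown. The range is about **7 to 83 of 120**. The lowest figure is a deliberate extreme: that shape has 1 − 0.1^(3/10) = 50% out by day 3, whereas Study procedure foresees discharge only after visit 4 at 72 h. Starting at day 3 gives 11.

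These counts precede the adverse-event condition. A patient with a grade 3–5 event within 10 days is a non-responder under either cut-off, so the number changing final responder status can only be equal or smaller.

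**The case against.** Several points on the other side have force.

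- **The visit 5 rules set timing and do not waive the hold.** They say when a form is completed, and the same section then refers back to the responder criteria. A reader might infer that Study procedure and Concomitant treatment make a day-9 or day-10 discharge a success. They do not say so; the second is a remark about clinical experience. Only the abstract words the endpoint without the hold, and it is a condensed summary that also omits grade 0 and the adverse-event condition. This stands. What remains is that no text says how the hold is confirmed after the discharge-day form.
- **Day 8 is one reading.** The 10-day limit could govern the adverse-event clause only, or the hold could start by day 10 and finish by day 12. The natural reading is still completion within 10 days, since the primary objective and Statistical methods {20a} tie efficacy to day 10. The other readings are open, so day 8 should not be called the definite deadline.
- **Readmissions are collected to 28 days after discharge,** and nothing forbids using them. This stands, and it makes the remedy cheap. However, Study procedure also ends participation for patients classed as treatment failures, so this information is not secure for everyone.
- **An unseen analysis plan may hold a derivation rule.** It may, but the conflict lies between statements in the protocol article, so it is more than absent detail.
- **Bias between arms.** A reader might infer that the cut-off would be chosen with discharge dates by arm in view. The trial is open-label, but {20a} blinds the analysing statistician to treatment, and one rule would apply to both arms. The documents do not show that such a choice would occur. They show only that the rule is not fixed.

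**Conclusion.** The point holds in this form. The primary outcome definition, read naturally, requires discharge by about day 8; the abstract accepts day 10; and the efficacy record is made on the discharge day with 0 h of the hold observed and no later confirmation stated. The 48-hour gap follows from the text alone.

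The effect on the response rate is unknown. With 90% discharged by day 10 of treatment, 7 to 83 of 120 patients could change class on the efficacy component, before the adverse-event condition. A reader might infer that a large part of the trial, 41 patients or more, must be reclassified. That follows only if discharges cluster on days 7–10 counted from treatment start. The documents do not establish this, and the 72-hour rule allows earlier discharge, which brings the number down to about 31, 11 or 7.

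The correction is needed because the text as written gives different primary-endpoint results for the same patient.

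**What to change.** 1. State one rule that says whether the 48-hour hold must start or be completed by day 10. One workable form: grade 0–2 first reached on or before day 10, with the patient alive and not readmitted during the following 48 hours. The documents do not dictate this choice over completion by day 10; what matters is that one is fixed.
2. Derive the hold from discharge, readmission and death dates, not from the form completed on the discharge day. Hospital records and visit 7 already supply these dates.
3. Classify patients only after the 48 hours have passed, including those in the interim analysis.
4. Align the abstract, the primary objective {7}, Primary outcomes {12}, the visit 5 rules in Study procedure, and the interim trigger {21b}.
5. Keep readmission and death follow-up for patients whose participation Study procedure would otherwise end as non-responders.
6. Report the other cut-off as a sensitivity analysis.

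The cost is wording in the protocol and analysis plan and one derived variable, with no new visit. Each patient's status becomes final up to 2 days later (day 12 at the latest under the form in item 1), and the interim data are delayed accordingly.
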